## Abstract

**Introduction:**

Previous trials finding an effect of self-monitoring on weight loss have considered the effect to be mediated by self-regulatory processes. However, a qualitative think-aloud study asking people to record thoughts and feelings during weighing showed that self-regulation occurs only rarely without further instruction. The aim of this trial is to test a novel intervention guiding people through the self-regulatory processes to see whether it facilitates weight loss.

**Methods and analyses:**

A parallel group, randomised controlled trial will be conducted to test the concept that a self-regulation intervention for weight loss increases weight loss compared with daily self-weighing without further support. One hundred participants with a body mass index ≥30 kg/m^2^ will be randomised to either the control or intervention group. The control group will be asked to weigh themselves daily for 8 weeks, the intervention group will be encouraged to follow the self-regulation intervention. They will be prompted to weigh daily, track their weight using an app, plan daily actions for weight loss and reflect on their action plans on a weekly basis. This self-regulation cycle will allow them to experiment with different weight loss strategies and identify effective and sustainable actions. Primary and process outcomes will be measured at baseline and 8 weeks’ follow-up. Linear regression analysis of the primary outcome, weight change, will assess the early effectiveness of the intervention. The process outcomes liking, perceived effectiveness, as well as usage and barriers with regard to the self-regulation intervention, will be assessed through qualitative analysis of follow-up interviews and quantitative analysis of adherence rates and responses to a final questionnaire.

**Ethics and dissemination:**

This trial was reviewed and approved by the NHS National Research Ethics Committee and the Health Research Authority (reference number: 18/SC/0482). The findings of the trial will be published in peer reviewed journals and presented at conferences.

**Trial registration number:**

ISRCTN14148239, prerecruitment.

**Protocol version:**

Version 1.1, 7 December 2018.

Strengths and limitations of this studyThis trial will provide preliminary evidence for whether a remotely delivered and iterative self-regulation intervention can enhance weight loss.The intervention addresses specific barriers to self-regulation, identified in a previous qualitative study of experiences of self-weighing.Process evaluation measures will assess participants liking, usage and perceived effectiveness of the intervention to enable future improvements.Blinding might be compromised as participants might be aware that they were assigned to the control or treatment group.The study is designed as a ‘proof-of-concept’ trial and longer-term studies will need to evaluate the effectiveness of the intervention as a weight management tool.

## Introduction

Self-monitoring of weight is often employed in multicomponent weight loss interventions, as evidence suggests it aids weight loss.^1–5^ The weight loss effect has often been ascribed to a self-regulation mechanism, based on the hypothesis that self-monitoring triggers self-regulation.^1 4–6^ In this context, self-regulation occurs in iterative cycles, starting by (1) contextualising the weight with previous measurements and goals, thus providing (2) an opportunity to reflect on previous behaviour and reinforce successful actions, enabling (3) the planning of actions to reach the goal, followed by (4) the performance of planned actions.^6–8^ This cycle of processes allows for experimentation with different weight loss techniques, helping the user to build a personal portfolio of effective and sustainable strategies.^9 10^

A study employing self-weighing as a standalone intervention did not find a significant weight loss effect, raising the question whether self-regulation is performed naturally after weighing or whether additional weight loss treatment components are necessary.^11^ We addressed this question in a think-aloud study, where twenty-four participants were asked to record their thoughts and feelings during daily weighing for 8 weeks, without being prompted to self-regulate.^12^ On 90% of occasions, participants contextualised their weight measurement, and on 58% participants reflected on previous behaviours. Only on 20% of occasions did participants plan actions and specific action planning, defining a concrete action and time plan, was rare (6%). The frequency of specific action planning was, however, significantly predictive of weight loss. Hence, the study provided support to the notion that completing the last step of the self-regulation process can elicit weight loss. However, the think-aloud study also showed that self-regulation does not occur autonomously, and that people need support in developing self-regulation skills, especially action planning. Self-regulation, once learnt, has the potential to be a weight loss strategy that is performed autonomously and sustainably. It provides an opportunity for remote weight loss interventions that do not require resource-intensive support from healthcare providers.

Several weight loss interventions including self-regulation components have been developed over the years. Some educate their users about self-regulation theory without providing active support for the key component—specific action planning.^1 4 13 14^ Others support users in action planning, but fail to imitate the iterative nature of self-regulation, as they do not allow the usage of self-monitoring feedback for adaptations to the action plans,^15–18^ thus disabling self-regulation. Some interventions guide participants through iterative reformulation of action plans following self-monitoring feedback, but are delivered through face-to-face sessions,^19 20^ which are resource-intensive and not easily rolled out at large scale. Other interventions incorporating action planning dictate which actions participants are supposed to follow,^15 21 22^ which might reduce goal ownership, a significant predictor of goal engagement and attrition.^23 24^ Notwithstanding these critiques, seven of the eleven studies cited here found significant weight loss, suggesting that components targeting the self-regulation cycle can enhance weight loss, encouraging further work in this area. Our critiques highlight the need for an intervention that guides participants through the whole and iterative self-regulation process in an autonomous, low-cost and scalable manner. Furthermore, since many interventions add self-regulation elements to a broader spectrum of weight loss treatment components,^14 17 25–27^ a study testing self-regulation as a standalone intervention is needed to investigate whether iterative self-regulation is sufficient to achieve weight loss.

With this study we aim to test the proof of concept of an intervention aiming to address this gap in the literature. The PREVAIL intervention (*P*eople *RE*gulating themsel*V*es to *A*chieve we*I*ght *L*oss) is a weight loss programme guiding people through the iterative self-regulation process. It encourages users to experiment with different weight loss approaches, and use the self-regulation mechanism to find their ideal set of tools.

### Objectives

The primary objective of this trial is to test the concept whether an intervention which trains individuals in self-regulatory processes, aids early weight loss in comparison to unsupported daily weighing. Other objectives pertain to the evaluation of usage and effectiveness of the self-regulation intervention components, as well as the qualitative analysis of participant experiences of the intervention.

## Methods

### Study design and setting

An individually randomised, two arm, parallel group design will be employed, assessing superiority of the self-regulation intervention over daily self-weighing alone. Participation will last 8 weeks. This length was deemed sufficient to assess early effectiveness of the intervention, as previous studies have been able to detect weight loss effects after 2 months.^28^ If the results are promising, the data will provide good evidence to justify conducting a longer-term randomised controlled trial. Participants will attend two study visits, one at baseline and one after the end of the eighth week of the intervention. The primary outcome will be weight change. The study will take place in Oxfordshire, UK, and run between April and October 2019.

### Recruitment

Two to four general practitioner (GP) practices around Oxford, UK, will function as participant identification centres and search their health records to identify suitable patients for the trial (age ≥18 years, body mass index (BMI) ≥30 kg/m^2^). The GP will screen the search list and exclude patients who would be inappropriate to invite, including terminally ill or violent patients. Suitable patients will be sent an invitation letter from their GP. They will be encouraged to contact the research team if they are interested in taking part. GPs may also identify suitable patients during routine consultations. We will ask practices not to refer participants to commercial weight loss programmes, other obesity clinics or bariatric surgery, while they are enrolled as participants in this trial.

### Eligibility criteria

#### Inclusion criteria

Participant is willing and able to give informed consent.Aged 18 years or above.BMI≥30 kg/m^2^.Owns an Apple or Android smartphone.

#### Exclusion criteria

The participant may not enter the study if any of the following apply:

Unable to understand English.Unable to follow all intervention procedures for a period of more than four consecutive days.Currently self-monitoring body weight more than once a week.Currently or within 3 months of study entry attended a weight management programme or currently participating in another weight loss study.Lost more than 5% of current body weight in the last 6 months.Prior bariatric surgery or scheduled for bariatric surgery.Pregnant or planning to become pregnant during the course of the study.Have an electronic medical implant, such as a pacemaker.Have ever had or been diagnosed with an eating disorder.People that the GP judges not able to meet the demands of either treatment programme or measurement schedule. This may include severe medical problems not listed above.

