### Randomisation and blinding

All eligible participants will be randomised with an allocation ratio of 1:1 to the intervention or control group. A randomisation sequence, stratified by GP and using block randomisation with randomly varying block sizes of 2 and 4 will be generated using a computer algorithm. Allocations will be concealed in numbered, sealed, opaque envelopes by an independent researcher in the department and handed to the researcher who will conduct the baseline visits.

Due to the nature of this trial, it will be difficult to blind participants to the treatment allocation. We will aim to make it as opaque as possible by presenting daily weighing as an intervention to control group participants, as done in previous trials.^29^ The researchers conducting baseline and follow-up will perform data analysis, and will not be blinded to treatment allocation. The primary outcome, weight change, will be measured objectively. Adherence to self-regulation steps will be measured objectively through the frequency of weight logs and completed questionnaires in control and intervention group. The evaluations of treatment components in the final questionnaire will be measured without researchers’ input and analysed quantitatively. Blinding of the researcher who conducts and analyses the semi-structured interviews with intervention group participants will not be possible.

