
10.1136/bmjopen-2019-031572.supp1Supplementary data

At baseline, participants will receive detailed instructions about the intervention with the aid of a manual which they may take home afterwards. The manual will explain the rationale of self-regulation and experimentation to participants and give tips on how to best weigh on a daily basis. It will also provide information on the different weight loss actions participants can try throughout the study. Participants will also be given an action diary, in which they will be asked to record their performed weight loss actions.

We will call participants at the end of the first and fourth week to ask about and solve any technical problems that may have arisen (eg, with the functioning of the scales or the receiving of questionnaires). A figure from the study manual depicting the intervention procedure is displayed in figure 2. The Template for Intervention Description and Replication (TIDieR) checklist^36^ for the PREVAIL intervention and the comparator is reported in table 1.

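### No rule stops two members of one household being allocated to opposite arms; if any such pairs enrol, those controls can be exposed to the intervention materials and lose their partial masking

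*Protocol article*

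**What the plan says.** **Recruitment.** In the protocol article, "Two to four general practitioner (GP) practices around Oxford, UK, will function as participant identification centres". They search their records for adults with a BMI of at least 30, and "Suitable patients will be sent an invitation letter from their GP". The GP may remove people unsuitable for invitation. No household check is described there, under Screening or under Baseline.

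**Eligibility.** The exclusion list begins "The participant may not enter the study if any of the following apply" and has ten entries. None refers to a relative or cohabitant already enrolled, and neither do the four inclusion criteria.

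**Allocation.** Under Study design and setting, "An individually randomised, two arm, parallel group design will be employed". Under Randomisation and blinding, participants are "randomised with an allocation ratio of 1:1 to the intervention or control group", with a sequence "stratified by GP and using block randomisation with randomly varying block sizes of 2 and 4". Household plays no part.

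**What goes home.** Under Intervention, "participants will receive detailed instructions about the intervention with the aid of a manual which they may take home afterwards". Intervention participants also get a paper action diary, and Table 1 describes the tracking app as free. The daily planning questionnaires and weekly trend feedback are emailed to the individual participant.

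**Masking.** Under Randomisation and blinding: "We will aim to make it as opaque as possible by presenting daily weighing as an intervention to control group participants". The strengths and limitations list already accepts that blinding may be compromised, without naming households.

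**The concern.** Adults who live together may well be registered at the same practice, so both can appear in its records search and both can be invited. If both enrol and are split, the control shares a home with material that explains the self-regulation rationale and describes the weight loss actions. Five of the seven action categories concern diet, so shared meals may change too. That control also learns that a fuller programme exists, which is what presenting daily weighing as an intervention is meant to obscure.

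The control condition is defined by the absence of further instruction, so the contrast between arms depends on keeping that absence intact. The plan protects it from outside sources: it excludes people in other weight loss studies or recent weight management programmes, and asks practices not to refer participants elsewhere. It has no matching protection against the trial's own active arm. An intention-to-treat analysis keeps the exposed control in the control arm and so carries the dilution into the estimate. In a proof-of-concept trial meant to inform a longer one, a difference diluted in this way could mislead that decision.

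**Working it through.** **Inputs.** From Sample size: 100 participants, 1.5 kg difference, SD 2.13 kg, 90% power, 20% drop-out. From Statistical analyses: two-sided 5%. From Randomisation and blinding: 1:1 allocation, blocks of 2 and 4 within practice. Assumed, because the documents do not give them: the number of split pairs *k*, and the fraction *f* of the 1.5 kg that an exposed control gains.

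**The plan's own figure.** Completers: 100 × 0.8 = 80, or 40 per arm. Standard error of the difference: 2.13 × √(2/40) = 0.476 kg. Power = Φ(1.5/0.476 − 1.96) = Φ(1.19) = 88.3% by the normal approximation (87.5% using the t distribution). That is close to the stated 90%. Reaching 90% takes 43 per arm, or 86 completers, and 86/0.8 = 107.5, so 108 recruited. The household point does not rest on this shortfall; 88.3% is only the reference value below.

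**Chance that an enrolled pair is split.** Suppose two household members are randomised back to back at one practice, and block sizes 2 and 4 are equally likely.
- A block of 2 starts two adjacent pairs: one inside the block (always split) and one across its end (split with probability 1/2). Expected splits: 1.5.
- A block of 4 starts four: three inside (each split with probability 2/3) and one across its end (1/2). Expected splits: 3 × 2/3 + 1/2 = 2.5.
- Averaged over block types, there are (1.5 + 2.5)/2 = 2 splits per (2 + 4)/2 = 3 adjacent pairs, that is 2/3. A simulation gave 66%.

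Simple randomisation would give 1/2, so small blocks within practice make a split somewhat more likely for people who enrol together.

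**Effect on the contrast.** With 50 controls randomised, *k* split pairs expose *k*/50 of them. The exposed share is assumed to be the same among completers. Expected difference = 1.5 × (1 − *f* × *k*/50); power = Φ(difference/0.476 − 1.96).

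| Split pairs *k* | Controls exposed | Difference, *f* = 0.5 | Power (loss in points) | Difference, *f* = 1 | Power (loss in points) |
|---|---|---|---|---|---|
| 0 | 0% | 1.500 kg | 88.3% | 1.500 kg | 88.3% |
| 1 | 2% | 1.485 kg | 87.7% (0.6) | 1.470 kg | 87.0% (1.3) |
| 2 | 4% | 1.470 kg | 87.0% (1.3) | 1.440 kg | 85.6% (2.7) |
| 5 | 10% | 1.425 kg | 84.9% (3.4) | 1.350 kg | 80.9% (7.4) |

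**The case against.** The strongest reply is that this argues from silence in a condensed article: the full protocol is not shown, and household members might be dealt with at invitation or screening. That possibility stands. Still, the article gives its exclusions as a list of what bars entry, and eligibility is not something a protocol leaves to an analysis plan. Followed as written, the plan permits split households.

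Four stronger readings are tempting, and the documents do not support them.

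- **That couples will often be invited and enrolled.** No household figure is given. Both people would need to meet every criterion and each contact the team, for a trial of only 100.
- **That the exposed control receives the whole intervention.** The daily questionnaires, the weekly trend emails with the linked reflection questionnaire, and the technical calls are directed to the intervention participant. A housemate might see some of this but is not sent it. The Introduction's own premise is that specific planning is rare without support (6% of weighing occasions), so seeing a manual need not confer the full effect.
- **That masking of the control arm fails.** Only controls living with an intervention participant lose it, and the plan already calls masking difficult and incomplete. Researchers also measure the primary outcome objectively, which limits reporting bias, though not a change in behaviour.
- **That the difference shrinks by 5 to 15%.** That needs 2.5 to 7.5 of 50 controls exposed, each gaining the full 1.5 kg. At a 2/3 split rate it takes about 4 to 11 enrolled household pairs, or 8 to 23 of the 100 participants; at 1/2 it takes 5 to 15 pairs, or 10 to 30 participants. Nothing in the documents supports such numbers.

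It is also fair to say that dilution toward zero would not create a false claim of superiority.

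**Conclusion.** The gap is real and its likely effect is modest. The eligibility, screening and randomisation text lets two members of one household be placed in opposite arms, and the small blocks within practice make this more likely than an even chance when they enrol back to back. Any control in such a pair can see the manual, diary and app, may share changed meals, and loses the partial masking. The most plausible result is a bias toward zero. The direction is not certain, since a disappointed control could also do worse.

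The size rests wholly on assumptions: the number of pairs is unknown and may be zero, and *f* is taken between one half and one. On that basis one or two split pairs cost 0.6 to 2.7 percentage points of power and five cost 3.4 to 7.4, from a reference of 88.3%. This is a cheap improvement worth making, not a flaw that threatens the trial's conclusion by itself.

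**What to change.** Add one exclusion criterion: another member of the household is, or has been, a participant in this trial. The first to consent stays eligible. Ask about it at the existing telephone or email screening.

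The cost is one line in the criteria, one screening question, and the loss of a few second household members from the recruitment pool. If the team prefers to keep them, it could allocate members of one household together and account for that in the analysis. This also closes the gap, but it complicates both the envelope-based allocation and the planned regression, so the exclusion is simpler.

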### Participant flow

#### Screening

People who are interested in taking part will contact the research team. The research team will then discuss study participation by telephone or email and undertake screening. If the person appears eligible and would like to attend a baseline visit, the research team will offer an appointment at a local venue. The participants will be emailed a participant information sheet (PIS).

#### Baseline

When the participants attend the baseline appointment, a member of the research team will seek informed consent and check eligibility for inclusion in the study by measuring height and weight for BMI calculation. The participants will be asked to complete an online questionnaire, capturing demographics (ie, age, gender, ethnicity) and previous experiences with self-weighing. Participants will be randomised and receive instructions for the assigned intervention. The researcher will provide participants with a body scale for the duration of the trial. A follow-up appointment will be scheduled for after the completion of the intervention period.

#### Follow-up

The aim of the follow-up appointment is to assess the outcomes of the trial. The research team will email participants in advance to remind them of the meeting. In the intervention group, this email will also contain a final questionnaire, asking participants about the usefulness of each of the intervention components and an overall rating of the intervention.

The appointment will be scheduled at a local venue and conducted by a member of the research team. Participants will be asked to return the body scales. The researcher will measure participants’ weight.

Twenty participants in the intervention group will be invited to participate in a semi-structured interview at the end of the follow-up meeting. The interviewees will be sampled by the lead researcher with the aim to reflect different levels of adherence, weight change and responses to the final questionnaire. Participants will be asked about their experiences with self-weighing, their liking of the intervention components and perceived barriers to engaging with the intervention. Interviews will be recorded, transcribed and analysed. A study flow chart is displayed in figure 1.

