### Sample size

We intend to recruit 100 participants, which is sufficient to detect a 1.5 kg difference between conditions, at 90% power and 5% type I error rate, while allowing for a 20% drop-out rate. Variance of weight change was based on results of a similar trial,^28^ which reported a SD of 2.13 kg at 2 months’ follow-up.

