#### Control

Participants in the control group will be instructed to self-weigh daily and see what daily weighing motivates them to do. They will not receive any further instructions. By using this comparator group, we want to test whether the self-regulation process can enhance self-weighing to be an effective weight loss tool. Participants will receive smart scales (BodyTrace, New York) which are equipped with a SIM card and automatically transfer measurements to a secure server via the 3G/4G network. This will allow us to assess adherence to daily weighing in the control group.

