#### Physical measurements

Participants’ height will be measured at baseline to the nearest 0.1 cm using a stadiometer. Weight will be measured both at baseline and follow-up using a digital scale (SC-240 MA, Tanita Japan). Weight will be recorded to the nearest 0.1 kg.

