### Retention

The daily questionnaire and weekly report emails will act as prompts for the participants to engage with the intervention. At the end of the follow-up visit, participants will receive a £35 one4all gift card.

There are no criteria for withdrawal other than participants’ request to withdraw. Participants can also ask to withdraw their collected data. We will ask participants wishing to withdraw whether they are willing to attend the final follow-up and take part in an exit interview to understand the reasons for their discontinuation.

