### Statistical analyses

The statistical analysis of the primary outcome, effectiveness of the intervention for weight loss, will be carried out on the basis of intention-to-treat (ITT). That is, after randomisation, participants will be analysed according to their allocated intervention group. We will endeavour to obtain full follow-up data on every participant to allow full ITT analysis. A linear regression, predicting weight at 8 weeks’ follow-up while adjusting for baseline weight and GP practice, will assess the effect of condition.^37^ We will assess the sensitivity of the analysis to different assumptions about missing data using a variety of imputation methods, including baseline observation carried forward analysis and an analysis of participants completing follow-up. A final analysis will impute the last home-measured weight for people who did not attend the final follow-up. All tests will be done at a 5% two-sided significance level.

Secondary outcomes will be analysed in several ways. Adherence rates will be assessed and compared between the experimental and control condition. Moderator analyses will assess the effect of adherence, highest educational qualification, liking of weighing at baseline, and overall intervention rating at follow-up (only intervention condition) on weight change.

Further exploratory analyses may be added post-hoc based on preliminary findings. The statistical analysis plan can be found in online supplementary appendix 2.

10.1136/bmjopen-2019-031572.supp2Supplementary data

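### The analysis that fills in missed visits with the last home weight sets no limit on the age of that weight, and home weights are captured differently in the two arms

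*Protocol article*

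**What the plan says.** All places are in the Protocol article.

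- **Follow-up:** "The appointment will be scheduled at a local venue and conducted by a member of the research team". The body scales lent for the trial are handed back at this same visit, so someone who does not come should still have one.
- **Physical measurements:** "Weight will be measured both at baseline and follow-up using a digital scale". This clinic weight is the basis of the primary outcome.
- **Retention:** people who withdraw are asked "whether they are willing to attend the final follow-up and take part in an exit interview". No weight reported from home is mentioned.
- **Statistical analyses:** the aim is stated as "We will endeavour to obtain full follow-up data on every participant to allow full ITT analysis". Sensitivity to missing data is examined by several methods, "including baseline observation carried forward analysis and an analysis of participants completing follow-up". Then: "A final analysis will impute the last home-measured weight for people who did not attend the final follow-up".
- **Control:** the smart scales "automatically transfer measurements to a secure server via the 3G/4G network".
- **Adherence measures and Table 1:** in the intervention arm a home weight is on record only if the participant entered it in the tracking app or the daily questionnaire. App data reach the team only when the participant sends a backup.
- **Sample size:** 100 participants, "while allowing for a 20% drop-out rate".

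**The concern.** Of the missing-data analyses that are named, the home-weight analysis is the only one that uses a non-attender's own data from after baseline. Its purpose is to stand in for the week-8 weight, yet the rule accepts any reading. A weight from week 2 counts the same as one from week 8.

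The recording route makes this more than a loose end. A control participant who keeps weighing leaves a current reading without doing anything further. An intervention participant who keeps weighing but stops typing leaves an old one. If the typical age of the substitute differs by arm, the analysis compares weights at different times after randomisation, and part of the estimated difference is then a difference in timing. A reader who relies on this analysis to judge whether the primary result survives missing visits could be reassured or alarmed for the wrong reason.

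A better value is within reach. Non-attenders should still hold a trial scale, and the team already emails participants before the visit.

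**Working it through.** **1. The plan's own figure.** Inputs from Sample size: difference 1.5 kg, SD 2.13 kg, 100 recruited, 20% drop-out, hence 40 per arm analysed. From Statistical analyses: two-sided 5%. Standard error = 2.13 × √(2/40) = 0.476 kg; 1.5/0.476 = 3.15; 3.15 − 1.96 = 1.19; power = 88.3% by the normal approximation, close to the stated 90%. This serves only to confirm the reading of the allowance as up to 20 people in 100. The point below does not rest on it.

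**2. Effect of the age of the reading.** The documents give no distribution of last-entry dates and no time course of loss, so the following are assumptions:

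- loss accrues linearly over 8 weeks;
- the true week-8 difference is 1.5 kg;
- a share d of each arm does not attend;
- the last readings fall at week w_I (intervention) and w_C (control);
- the 8-week losses are L_C (0 or 1 kg) in controls and L_I = L_C + 1.5 in the intervention arm.

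Understatement of the difference = d × [L_I × (1 − w_I/8) − L_C × (1 − w_C/8)].

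With d = 0.20:

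| Last reading, intervention / control | Understatement, L_C = 0 | Understatement, L_C = 1 kg | Estimated difference |
|---|---|---|---|
| week 8 / week 8 | 0 | 0 | 1.50 kg |
| week 4 / week 8 | 0.15 | 0.25 | 1.35 to 1.25 kg |
| week 2 / week 8 | 0.23 | 0.38 | 1.28 to 1.13 kg |
| week 4 / week 4 | 0.15 | 0.15 | 1.35 kg |
| week 8 / week 4 | 0 | −0.10 | 1.50 to 1.60 kg |

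With d = 0.10 every shift halves. The fourth row shows that old readings distort the estimate even when their age is equal in both arms. The last row shows that older control readings leave the difference unchanged or overstate it.

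**3. A spread of dates.** Suppose intervention entries end uniformly over the 8 weeks and controls are read to week 8. The carried value then holds on average half of the 8-week loss L, so the understatement is 0.20 × 0.5 × L. For L = 1.5 kg this is 0.15 kg; for L = 3 kg it is 0.30 kg. Against the 1.5 kg design difference these are 10% and 20%.

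**4. Early loss that is regained.** Keep the same uniform dates, and let 1.5 kg be lost in a straight line by mid-trial and fully regained by week 8. The mean carried loss is 0.75 kg while the true week-8 loss is zero, so the effect is overstated by 0.20 × 0.75 = 0.15 kg.

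**The case against.** **It touches one supporting analysis.** This stands. The primary outcome is measured on the clinic scale, and the home-weight analysis sits beside baseline carried forward and completers. A reader might infer that the trial's main result is biased by these amounts; the documents do not support that. Nor is the shift large beside what the plan already accepts: with a 1.5 kg difference and 20% missing in each arm, baseline carried forward attenuates by 0.20 × 1.5 = 0.30 kg.

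**The direction is not known.** This stands too. A reader might infer from manual entry that intervention readings will be the older ones. However, that arm gets a questionnaire every morning that begins by asking for the weight, a weekly report email, and calls at the end of weeks 1 and 4. Controls get no further instructions, and automatic upload helps only if someone steps on the scale. Either arm could have the older readings.

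**No power is gained for the primary comparison.** Correct. Recovering half of the non-attenders would raise t-test power from 87.5% (40 per arm) to 91.0% (45 per arm), but only if home readings entered the primary comparison as exactly as clinic weights. Here they do not enter it. The response rate of one half has no source in the documents either.

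**The 20% is an allowance.** It is not a forecast that 20 outcomes will be missing; the plan aims for full follow-up and lists retention steps, including a gift card at the visit.

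**An article leaves such detail to other documents.** This stands in part. The full protocol may describe another route to the weight, and the analysis plan in the supplementary appendix, which is not shown, may set a date window. Silence on these is no error. What remains is a rule that the article does state: it takes the last reading whatever its age.

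**Conclusion.** The point holds in a limited form. As written, the home-weight analysis can substitute readings of any age, and because capture differs by arm it may compare different time points between arms. The likely size is modest: an understatement of 0.15 to 0.30 kg under linear loss of 1.5 to 3 kg, 20% non-attendance, uniform last entries in the intervention arm and current readings in controls. It is half that at 10% non-attendance, and of opposite sign if control readings are the older or early loss is regained. These are illustrations on stated assumptions and apply to that analysis alone. The documents do not support a claim of bias in the primary measurement, of a known direction, or of lost power in the primary comparison. The case for change is that a better value can be had cheaply, and only while participants still hold the scales.

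**What to change.** **Follow-up section.** Add that everyone who does not attend, in both arms and with identical wording, is asked by email or phone, before the scale is returned, for one dated morning weight on the trial scale in the week after week 8.

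**Statistical analyses section.** In the home-weight analysis, use that requested reading first. If there is none, use a home weight recorded within 7 days of the end of week 8. Report by arm how many such readings were available and how old they were. Keep the clinic weight as the primary measurement.

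The order matters. A 7-day window alone could admit automatic control uploads while excluding intervention participants who had stopped typing, turning a difference in age into a difference in missingness between arms. The same active request in both arms is what guards against this; the window is secondary.

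**Cost.** One message template, and at most about 20 short contacts if the allowance is reached (0.20 × 100). A home reading is less exact than a clinic weight, which is acceptable because it stays in a supporting analysis.
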